### Data analysis

All data analyses will be conducted according to the intention-to-treat principle, and the analysis will be performed in a double-blind manner by qualified statisticians. The EpiData 3.1 software will be used to build the database, and missing data will be replaced with the mean or median of the item for the homogeneous participant population according to complete data. Two similar participants with complete data will be subjected to repeated review, and a logic check will be performed to confirm that the data are correct before analysis.

The data will be analyzed using the Statistical Package for the Social Sciences version 17.0 (SPSS 17.0). Measured data will be expressed as the mean, median, minimum, and maximum values. Comparisons between the two groups will be analyzed by analysis of variance and pairwise comparisons (univariate variance will be assessed with the rank-sum test). Count data will be expressed as the composition ratio and the rate. Between-group efficacy will be assessed using the χ^2^ test, and ranked data will be analyzed with the rank-sum test. A baseline comparison test will be performed at a significance level of α = 0.10, and an efficacy analysis will be performed at a significance level of α = 0.05.

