### Sample size calculation

This study is mainly focused on determining the efficacy of BMF for AR patients with LSQDS. The primary outcome is the TNSS. With reference to data from a previous study [46] and our clinical observations, the sample size was calculated using the noninferiority test for two means with software PASS 2011. We assumed that the TNSS of the treatment group will be 5.53 ± 2.79 and that of the control group will be 6.64 ± 3.06. To obtain a significance level of 5%, a power of 90%, and a noninferiority margin of 0.92, 74 participants are required. Allowing for an 8% dropout rate, 80 participants are needed, with 40 in each group.

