### Criteria for stopping treatment

A participant may stop treatment and withdraw from the research project for any reason at any time, and the reason for the withdrawal will be recorded in their CRF. The participants will be told that they have the right to withdraw from the trial and that they will be provided with standardized treatment if they withdraw.

The criteria for stopping treatment and withdrawing from the research project are:The participant has suffered an AE related to taking the drug, and the investigator believes it is not appropriate for them to continue taking the drug.The participant is diagnosed with asthma or other complications of AR during the study.The participant develops another severe disease that needs to be treated during the study.Poor compliance, such that the actual drug usage is less than 80% or more than 120% of the prescribed dose.Use of drugs proscribed for AR during the study.

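### The trial is sized for noninferiority, but every analysis is placed under intention-to-treat, which leaves no per-protocol check and modestly raises the risk of a false noninferiority claim

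*Protocol article*

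**What the plan says.** Under Sample size calculation, "the sample size was calculated using the noninferiority test for two means with software PASS 2011". The inputs are "We assumed that the TNSS of the treatment group will be 5.53 ± 2.79 and that of the control group will be 6.64 ± 3.06", with "a power of 90%, and a noninferiority margin of 0.92, 74 participants are required". The comparator is active: the Background explains that levocetirizine was chosen in place of placebo.

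Under Data analysis, the population is fixed in one sentence: "All data analyses will be conducted according to the intention-to-treat principle". The article names no other analysis set. For gaps in the data, "missing data will be replaced with the mean or median of the item for the homogeneous participant population according to complete data". The tests listed there are ordinary between-group comparisons at 0.05, and the margin of 0.92 does not reappear.

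Criteria for stopping treatment lists, among the reasons for stopping and withdrawing, "Poor compliance, such that the actual drug usage is less than 80% or more than 120% of the prescribed dose", and also the use of AR drugs that the protocol forbids. Under Interventions, desloratadine is available as rescue in both arms and its use is to be recorded and analysed.

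**The concern.** Intention-to-treat is the cautious choice when the aim is to show a difference, because patients who leave their assigned treatment blur the contrast and make success harder. When the aim is to show that a new treatment is not worse by more than a margin, the same blurring usually makes success easier. Regulators and reviewers therefore commonly ask for a per-protocol analysis alongside intention-to-treat in a noninferiority trial.

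The article does more than omit a detail that an analysis plan could supply. The word *all* fixes a single population for a trial sized on a noninferiority hypothesis. The raw material for a second set exists (compliance limits, a proscribed-drug rule, a medicine diary, return of unused drug) but is used only to stop treatment and withdraw patients. At stake is whether a noninferiority result could be shown not to depend on imperfect adherence.

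**Working it through.** **1. Reproduce the plan's sample size.** The common SD is √((2.79² + 3.06²)/2) = √8.574 = 2.928. The assumed difference is 5.53 − 6.64 = −1.11 (BMF better), so the distance from the margin is 0.92 + 1.11 = 2.03.

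- Normal formula, one-sided 5%, 90% power: n = 2 × 8.574 × (1.645 + 1.282)² / 2.03² ≈ 35.6, so 36 per arm.
- With the t distribution: 37 per arm, 74 in total. This matches the stated figure.
- One-sided 2.5% gives 44 per arm (45 with t), which does not match.

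The plan is therefore a noninferiority design at one-sided 5%, although the article does not state the sidedness.

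**2. Dilution in both arms.** Inputs: 40 per arm from "Allowing for an 8% dropout rate, 80 participants are needed, with 40 in each group"; the stated SDs; BMF truly worse by exactly 0.92 among adherers; a share f of each arm off its drug, with the same expected outcome in both arms. The article does not give f. The 8% dropout is used as one anchor; the larger values are assumptions.

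SE = √((2.79² + 3.06²)/40) = √(17.148/40) = 0.655. The intention-to-treat difference becomes 0.92(1 − f), so the false noninferiority rate is Φ(−1.645 + 0.92f/0.655).

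| f | Diluted difference | False noninferiority |
|---|---|---|
| 0 | 0.920 | 5.0% |
| 8% (stated dropout) | 0.846 | 6.3% |
| 20% (assumed) | 0.736 | 8.6% |
| 30% (assumed) | 0.644 | 11.1% |

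**3. If the patients are withdrawn and imputed instead.** Simulation with 100,000 replicates, 40 per arm, true difference 0.92, withdrawal at random:

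| Withdrawn per arm | Arm-mean imputation | Pooled-mean imputation | Observed patients only |
|---|---|---|---|
| 3 of 40 | 6.3% | 6.2% | 4.9% |
| 8 of 40 | 9.6% | 9.4% | 5.1% |

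The pooled mean pulls the arms together. The arm mean leaves the difference alone but makes the variance too small. The article does not make clear which is meant.

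**4. Requiring both sets to agree.** Under the model of step 2, with exclusion unrelated to outcome, per-protocol alone stays at about 5% and the joint requirement gives about 4% for f from 8% to 30%.

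**5. If BMF really is better by 1.11.** Dilution then lowers power. At 40 per arm it is Φ(2.03/0.655 − 1.645) = 92.7% with f = 0, and Φ((0.92 + 0.888)/0.655 − 1.645) = 86.8% with f = 20%.

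**The case against.** Six points can be made against the concern.

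- **Withdrawal.** Poor compliers and users of forbidden drugs are to be withdrawn, so their later TNSS may be missing and not observed and convergent. This stands in part: some of the effect then belongs to imputation (step 3). It does not remove all of it, because unused drug is returned only at the end of the study and some poor compliers may be recognised after their TNSS is recorded.
- **No margin test.** The Data analysis section lists only difference tests, for which dilution works against a positive result. This stands. The harm arises only once a comparison with 0.92 is made, so the fix has to supply that comparison too.
- **Direction.** If non-adherence occurs only in the BMF arm and those patients do 1 point worse (an assumption), the rate falls: Φ(−1.645 − 0.08/0.655) = 3.9% at 8% and Φ(−1.645 − 0.20/0.655) = 2.6% at 20%. The bias is typical, not certain.
- **Partial compliers.** Someone at 75% of the prescribed amount counts as non-compliant but still receives treatment, so giving all such patients zero difference overstates dilution.
- **Per-protocol is not a safe harbour.** A reader might infer that it holds 5% in general. It does so only if exclusion is unrelated to outcome. With 6 BMF and 3 control patients excluded and exclusion correlated 0.3 to 0.5 with worse TNSS (all assumed), simulation gives 6.6% to about 8%.
- **Unseen analysis plan.** Supporting sets are often specified there. The word *all* weakens this defence, since a second set would depart from the published sentence, but stating the principle need not forbid a sensitivity analysis.

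**Conclusion.** The point holds in a moderate form. A trial sized for noninferiority against an active drug commits all its analyses to intention-to-treat and so has no per-protocol check. With off-drug patients in both arms, the false noninferiority rate goes from 5% to about 6.3% at the only share the article can anchor (8%, its dropout figure) and to about 8.6% at an assumed 20%. These figures assume a true deficit equal to the margin, one-sided 5%, 40 per arm, and no treatment difference among off-drug patients.

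A reader might infer that the plan doubles the error rate, or that a worse BMF would readily pass. The documents do not support that: nothing in them indicates 20% to 30% non-adherence, adherence by arm is not given, and the written tests never use the margin. Nor do they support replacing intention-to-treat with per-protocol, since per-protocol exclusions may themselves be related to outcome. The change is worth making because it is standard for this design and cheap, not because a large bias has been shown.

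**What to change.** In Data analysis, replace the blanket sentence with text to this effect:

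- The difference in end-of-treatment (week 4) TNSS and its confidence limit are compared with the margin of 0.92. The article lists several TNSS assessments and names none as primary, so this visit has to be stated.
- The comparison is made in the intention-to-treat set and in a per-protocol set defined before unblinding: usage within 80% to 120% of prescribed, no proscribed AR drug, week-4 TNSS observed.
- Noninferiority is claimed only if both sets agree.
- Rescue desloratadine use is reported by arm, with a sensitivity analysis for it. It is permitted in both arms, so the per-protocol set does not remove that source of convergence.

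The cost is a paragraph of text and some extra analysis runs. The article already provides for recording drug usage and rescue use, and no added patients or visits are needed. The downside is slightly lower power, because two sets must agree. Keeping intention-to-treat alongside guards against per-protocol exclusions that are related to outcome.

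### Filling missing scores with one mean or median and testing them as observed makes intervals too narrow and lifts the noninferiority error from 5% to about 6.4% at the planned dropout

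*Protocol article*

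**What the plan says.** The Data analysis section of the protocol article gives one rule for all missing data: "missing data will be replaced with the mean or median of the item for the homogeneous participant population according to complete data". It does not say whether the reference population is the patient's own arm or both arms together, or when the mean applies and when the median.

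The same section states that "All data analyses will be conducted according to the intention-to-treat principle", so a participant without an outcome stays in the analysis as a filled value. On testing it says "Comparisons between the two groups will be analyzed by analysis of variance and pairwise comparisons", with rank-sum tests as the alternative, and that "an efficacy analysis will be performed at a significance level of α = 0.05". It mentions no variance correction, model-based method or sensitivity analysis next to the filling rule.

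The Sample size calculation section supplies the planning figures. Losses are covered by enlarging the trial: "Allowing for an 8% dropout rate, 80 participants are needed", which makes 40 per arm. The number before that enlargement rests on a noninferiority comparison, described in these terms: "To obtain a significance level of 5%, a power of 90%, and a noninferiority margin of 0.92, 74 participants are required". The planning values behind it are a mean TNSS of 5.53 (SD 2.79) under BMF and 6.64 (SD 3.06) under control.

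**The concern.** A value filled at the mean adds nothing to the sum of squares but counts as a full patient in n. The standard deviation falls, n is overstated, and the two errors multiply. The sample size section adds participants because dropouts are expected to yield no evaluable score; the analysis section then counts those same dropouts as evaluable.

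The filled value also takes no account of the patient. Under Outcome measurement, TNSS is recorded at the beginning, middle and end of treatment and monthly in follow-up, so most dropouts will have a baseline score and some a mid-treatment score. The rule ignores both.

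If the mean is taken over both arms, the filled values are identical in each arm and pull the difference toward zero. At stake is the error rate of the primary comparison: the chance of declaring BMF noninferior on TNSS when it is worse by the full margin.

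**Working it through.** **Inputs** (Sample size calculation section): SD 2.79 (BMF) and 3.06 (control); assumed means 5.53 and 6.64, so 1.11 in favour of BMF; margin 0.92; significance level 5%; power 90%; 8% dropout; 40 randomised per arm. Since 8% of 40 is 3.2, the nearest whole number is 3 missing and 37 observed per arm (7.5%).

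**1. The plan's own figure.** Root-mean-square SD = sqrt[(2.79² + 3.06²)/2] = 2.93. Distance from the assumed effect to the margin = 0.92 + 1.11 = 2.03. Normal formula: n per arm = 2 × (1.645 + 1.282)² × 2.93² / 2.03², which rounds up to 36. The t version gives 37 per arm, 74 in total, with power 90.5%. This matches the stated 74, but only for a one-sided 5% test; one-sided 2.5% needs 88 (normal) or 90 (t). One-sided 5% is therefore the main case below.

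**2. Standard error after same-arm filling.** With k of 40 observed per arm, the sum of squares comes from k values but is divided by 39, and the variance of the mean is divided by 40 instead of k:

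SE ratio = sqrt[((k − 1)/39) × (k/40)]

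- k = 37: sqrt(0.9231 × 0.925) = 0.924, about 8% too small.
- k = 34 (15% missing): sqrt(0.8462 × 0.85) = 0.848.

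**3. Error rate by formula.** True one-sided error ≈ 1 − Φ(1.645 × ratio): 1 − Φ(1.520) = 6.4% at k = 37, and 1 − Φ(1.395) = 8.2% at k = 34.

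**4. Simulation check.** 200,000 trials per scenario, 40 per arm, normal scores with the protocol's SDs, true difference exactly 0.92, whole scores missing completely at random and equally in both arms, pooled t test. False noninferiority at nominal one-sided 5%:

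| Missing | Same-arm mean | Pooled mean |
|---|---|---|
| 5% | 5.8% | 5.8% |
| 7.5% | 6.4% | 6.4% |
| 10% | 7.0% | 6.7% |
| 15% | 8.1% | 7.9% |
| 20% | 9.4% | 9.3% |
| 30% | 12.7% | 12.9% |

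Complete-case analysis of the same data stays at about 5% throughout. At a nominal 2.5% with 37 observed per arm, the rates are 3.5% (same arm) and 3.3% (pooled).

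**5. Intervals at 37 of 40.** Complete-case: mean 95% width 2.71, coverage 95.0%. Same-arm fill: width 2.50, coverage 93.0%. Pooled fill: width 2.50, coverage 94.8%. The pooled interval looks nearly right overall, but its misses are lopsided: of the 5.2% total, 3.3% fall on the side that declares noninferiority.

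**6. Shrinkage under a pooled mean.** The difference is multiplied by k/40: 0.92 × 0.925 = 0.85 at 7.5% missing, and 0.92 × 0.85 = 0.78 at 15%.

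The simulation covers filling with the mean. Filling with the median was not run separately; the mechanism is the same.

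**The case against.** A reader might go further and infer that the rule biases the trial toward noninferiority, because patients who leave with poor control receive an average completer's score. The documents do not support this as a general claim.

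- It needs BMF to lose more poor responders than control, and nothing in the article says so. The Criteria for stopping treatment section lists adverse events, complications, another severe disease, compliance and proscribed drugs, but not lack of efficacy. The Interventions section provides rescue medication, so poor control need not mean withdrawal.
- Under an assumed loss of the worst 10% of BMF and worst 5% of control scores, same-arm filling gives about 14% false noninferiority, but complete-case analysis already gives about 12%. At 15% against 5% the figures are about 24% and 20%. Most of the excess comes from the assumed dropout pattern, not from the filling.
- With the arms swapped, filling gives 3.5% and 1.8%, below nominal.

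The pooled-mean point also has limits. Shrinkage helps noninferiority only if BMF is truly worse. Under the plan's own assumption it moves the estimate toward the margin (−1.11 × 0.925 = −1.03), and at the margin pooling adds essentially no error beyond same-arm filling.

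Other points that stand: the effect is smaller if only single items of a score are missing; the article says the analysis is done blind, and a statistical analysis plan may settle mean against median; and noninferiority is named only in the sample size section, so the error rates refer to the test on which the sample size was built.

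None of this rescues the rule. It is stated outright, so it is not detail deferred to a later document. It raised the error above nominal at every level of random missingness examined, under both readings of the reference population.

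**Conclusion.** The concern holds, at modest size. At about the planned dropout the standard error is about 8% too small, 95% coverage is about 93% with same-arm filling, and a one-sided 5% noninferiority test at the 0.92 margin has a true error of about 6.4%. At 15% missing, which is not a planning figure, the error is about 8%. These results assume whole TNSS scores missing completely at random and equally by arm, and that filled values are analysed as observed. The last is inferred from the named tests and the absence of any correction; nothing in the article contradicts it.

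Outcome-related dropout could bias the comparison in either direction. Its size cannot be derived from the document, and most of it would remain in a complete-case analysis. This should be fixed; it does not undermine the design.

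**What to change.** Delete the mean or median rule for missing outcome scores. Replace it with one of two methods, chosen before unblinding:

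- a mixed model for repeated measures on observed TNSS at all post-baseline visits, with treatment, visit, treatment by visit and baseline TNSS, and no imputation; or
- multiple imputation within arm using baseline and mid-treatment TNSS, with standard errors that reflect the imputation.

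Both assume that missingness is explained by the observed data. A tipping-point analysis, in which missing BMF scores are made progressively worse, should therefore be reported as supportive, without a pass or fail requirement.

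The cost is analysis wording and a little programming. Intervals become slightly wider (in the random-missingness check at 37 per arm, complete-case width 2.71 against 2.50 when filled). No new patients, visits or data are needed, and the planned sample size does not change, because it already rests on 37 evaluable per arm (74/2).

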Most CHM is administered orally, whereby formulations are ingested, transferred, digested, and absorbed through the gastrointestinal system. Accordingly, CHM may influence the gastrointestinal system, including the intestinal mucosa and gut microbiota, the latter of which is essential for health and closely linked to diseases [23]. For instance, several studies have demonstrated that low gut microbiota diversity is associated with a high risk of allergic diseases [24–28]. Other studies have reported that the characteristics of seasonal AR include a lower diversity of intestinal *Bifidobacterium* [29], with a reduction of *Bifidobacterium*, *Clostridium*, and *Bacteroides* [30] and increased populations of *Bacteroides fragilis* [31]. A few systematic reviews and studies indicate that certain probiotics are beneficial for patients with AR [32–35]. We hypothesize that components of CHM, such as glycosides and oligosaccharides [36], may influence the gut microbiota in the same manner as an oral probiotic by regulating local intestinal immunological conditions and thereby, achieving systematic immunomodulation [37, 38].

Placeboes have been widely used in the control groups of previous clinical studies of AR treated with pharmacotherapy and immunotherapy, with the placebo control treatment resulting in over 50% symptom relief [6]. Therefore, in this study, we selected Western medicine as the positive control instead of a placebo. Levocetirizine, a second-generation antihistamine that acts on peripheral histamine H1 receptors, has a strong anti-allergic effect without a sedative effect, and it is used for relieving and preventing not only AR symptoms but also those of other allergic diseases. After careful consideration of the adverse effects and the desired effect, we chose levocetirizine as the intervention for the control group.

To blind the participants and the researchers adequately, a placebo for the intervention given to the other group will be administered to both groups. We designed a double-blind, double-dummy RCT for AR patients with LSQDS. The objectives are to assess the efficacy of BMF for AR patients with LSQDS and to explore the mechanism of BMF in treating AR with respect to the immune response and gut microbiota.

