### Outcome measurement

The primary outcome is a change in the Total Nasal Symptom Score (TNSS) [40]. Secondary outcome measures are as follows: (1) changes in the standard version of the Rhinoconjunctivitis Quality of Life Questionnaire (RQLQ(S)) score; (2) the frequency of AR episodes and their severity (visual analog scale, VAS); (3) changes in the serum levels of cytokines IL-4, interferon-γ (IFN-γ), transforming growth factor β-1 (TGF-β1), and interleukin-17 (IL-17), and changes in the gut microbiota composition in stools before and after treatment. In addition, participants will complete a medicine diary and report any AEs related to the intervention drugs throughout the trial.

The TNSS evaluates the following four nasal symptoms: rhinorrhea, nasal obstruction, nasal itching, and sneezing. The symptoms are self-assessed and recorded by subjects using a four-point scale (0 = no symptoms, 1 = mild symptoms, 2 = moderate symptoms, and 3 = severe symptoms), with low scores indicating less severe nasal symptoms [40]. The RQLQ(S) is a disease-specific questionnaire that can assess quality of life impairment in AR patients. This questionnaire consists of 28 questions covering the following seven domains: activities, sleep, non-nose/eye symptoms, practical problems, nasal symptoms, eye symptoms and emotional problems [41]. The RQLQ(S) with standardized activities is an updated version of the original RQLQ [42]. It has been translated into different languages and has frequently been used in different countries. The VAS, which ranges from 0 (nasal symptoms not at all bothersome) to 10 (nasal symptoms extremely bothersome) was designed to assess the severity of nasal symptom disturbance and has been validated for use in the quantitative evaluation of AR severity [43]. The TNSS, RQLQ(S), and frequency and severity of AR episodes will be evaluated at the beginning of, middle of and after the treatment period and at the end of each month during the 3-month follow-up period (Fig. 2).

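### The trial is sized for a noninferiority test with a margin of 0.92, but the between-group tests named in the analysis section all test for no difference and never use the margin

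*Protocol article*

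**What the plan says.** In the protocol article, under Sample size calculation, "the sample size was calculated using the noninferiority test for two means with software PASS 2011". The inputs are that "the TNSS of the treatment group will be 5.53 ± 2.79" and "that of the control group will be 6.64 ± 3.06", and the result is that for "a significance level of 5%, a power of 90%, and a noninferiority margin of 0.92, 74 participants are required". An 8% dropout allowance takes this to 80, or 40 per group. Noninferiority and the margin appear nowhere else in the article.

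Under Data analysis, the methods for measured data are given as "Comparisons between the two groups will be analyzed by analysis of variance and pairwise comparisons", with a rank-sum alternative. After count data are described, the text continues: "Between-group efficacy will be assessed using the" chi-square test, with rank-sum for ranked data. Efficacy is tested at α = 0.05, with sidedness not stated. The section mentions no margin, no confidence interval for the treatment difference and no noninferiority decision rule. Under Outcome measurement the primary outcome is a change in TNSS, "with low scores indicating less severe nasal symptoms". The objective at the end of the Background is to assess efficacy.

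**The concern.** The hypothesis that justified 80 patients is that BMF is not worse than levocetirizine by 0.92 or more. Analysis of variance, rank-sum and chi-square tests ask whether the groups differ at all. A non-significant answer to that question is compatible with BMF being better, equal, or worse by more than the margin, so it does not answer the question the trial was sized for.

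The comparison with levocetirizine carries particular weight because there is no placebo arm. The Background reports earlier placebo-controlled studies "with the placebo control treatment resulting in over 50% symptom relief", so improvement within the BMF group would say little by itself. If the between-group comparison is then run as a difference test, the trial has no stated rule for its most plausible useful conclusion.

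**Working it through.** **Inputs** (Sample size calculation unless noted): means 5.53 (BMF) and 6.64 (control); SDs 2.79 and 3.06; margin 0.92; significance level 5%, sidedness not stated; power 90%; 74 evaluable (37 per arm), 80 with dropout (40 per arm). Lower scores are better (Outcome measurement).

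**Common quantities**
- Assumed difference, BMF minus control: 5.53 − 6.64 = −1.11, in favour of BMF.
- Pooled SD = √[(2.79² + 3.06²)/2] = √[(7.784 + 9.364)/2] = √8.574 = 2.928.
- Standard error = 2.928 × √(2/n): 0.681 at 37 per arm, 0.655 at 40 per arm.

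**Step 1: reproduce the stated 74.** The distance from the assumed difference to the margin is 0.92 − (−1.11) = 2.03. Power is P(T > t(1−α, 2n−2)), where T is noncentral t with noncentrality 2.03/SE.
- 37 per arm: 2.03/0.681 = 2.98. At one-sided 5%, power is 90.5%.
- 36 per arm: 89.8%, just short of 90%.
- At one-sided 2.5%, 37 per arm gives 83.7%. The normal approximation then needs 44 per arm (88 in total).

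So 74 is reproduced exactly at one-sided 5% and not at one-sided 2.5%.

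**Step 2: power of the difference test on the same inputs.** The noncentrality is now 1.11/SE.

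| Test | 37 per arm | 40 per arm |
|---|---|---|
| Noncentrality | 1.63 | 1.70 |
| Two-sided 5%, t | 36.3% | 38.8% |
| Two-sided 5%, normal approximation | 37.1% | 39.6% |
| Two-sided 5%, rank-sum (simulated, normal data) | 35% | 37.5% |
| One-sided 5%, t | 48.8% | 51.4% |

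**Step 3: what a non-significant result would mean.** If BMF were truly worse by 0.92, the noncentrality at 37 per arm is 0.92/0.681 = 1.35. The two-sided 5% test is then non-significant with probability 1 − 0.266 = 73.4%.

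**Step 4: sensitivity to the SD.** The primary outcome is a change, and its SD is not given. Taking illustrative SDs (assumptions, not protocol figures), a 1.11 difference at 37 per arm has two-sided 5% power of 65% with SD 2.0, 47% with SD 2.5 and 27% with SD 3.5.

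**Step 5: noninferiority power under the two usual confidence levels**, with the protocol's inputs.

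| Rule: upper limit below +0.92 | 37 per arm | 40 per arm |
|---|---|---|
| Two-sided 90% CI (one-sided 5%) | 90.5% | 92.3% |
| Two-sided 95% CI (one-sided 2.5%) | 83.7% | 86.5% |

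**The case against.** The strongest reply is that the Data analysis section is a general paragraph covering measured, count and ranked data, that it labels no test as primary, and that the margin, level and power are already fixed under Sample size calculation. An analysis of variance yields the mean difference and standard error needed to apply the margin, and an analysis plan not shown here may state the rule. Part of this stands: a missing decision rule alone would be no finding. But the article does more than stay silent. It names the tests for between-group efficacy, and they address a different hypothesis from the one used for sizing. The two sections need reconciling whatever another document says.

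Several stronger readings are tempting and are not supported:
- That the plan cannot deliver noninferiority at all. A significant analysis-of-variance result favouring BMF puts the whole interval below zero, hence below +0.92.
- That power is simply under 40%. This needs a two-sided test, which is the natural reading of analysis of variance but is not stated, and the score SDs. Nor does it contradict the stated 90%, which refers to noninferiority and reproduces.
- That the 95% half-width (1.993 × 0.681 = 1.36) exceeds the margin and so condemns the analysis. It would be the same under a margin test, and at the assumed difference the upper limit is −1.11 + 1.36 = +0.25, below 0.92.
- That the chi-square test is misapplied to TNSS. The text introduces it with count data and does not assign it to TNSS; under Interventions, rescue medication use is to be analysed as an indicator of effect, which could be a count outcome.
- That only a margin test gives a controlled claim. Superiority over a randomised, blinded active control is one too.
- That the investigators would report a null result as equivalence. The article does not say so; it only leaves the possibility open.

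**Conclusion.** The point holds as a contradiction between two sections of the article. The sizing is a genuine noninferiority calculation, reproduced at one-sided 5%; the named between-group tests are tests of no difference that leave the margin unused. As written, noninferiority would be shown only through a significant BMF advantage, with power of about 36% to 39% on the protocol's means and SDs if the test is two-sided at 5%, or 49% to 51% if one-sided at 5%. Those percentages depend on score SDs standing in for the unreported SD of change and could move either way. The mismatch of hypotheses depends on none of them. It should be corrected before unblinding because the primary conclusion rests on it.

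**What to change.** In the Data analysis section, state that:
- the primary analysis estimates the BMF minus levocetirizine difference in the protocol's primary outcome, the change in TNSS, at a named time point, with a confidence interval;
- noninferiority is concluded only if the upper confidence limit is below +0.92, at the level that matches the sizing (one-sided 5%, i.e. a two-sided 90% interval);
- superiority (upper limit below 0) is tested only after noninferiority is shown;
- a non-significant difference is not evidence of noninferiority.

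State the sidedness of the 5% under Sample size calculation as well. If a two-sided 95% interval is preferred, restate the noninferiority power as about 84% (74 evaluable) to 86% (80); that option has a power cost, not just a wording cost.

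The matching-level option changes only text: same patients, same data. The alternative, declaring a superiority trial, would need about 147 per arm by the normal approximation, 294 evaluable (320 with 8% dropout), for 90% power to detect 1.11 with SD 2.928. With 76 patients already recruited according to Trial status, that is not practical.
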